The control group will wear an activity tracker wristband with a display covered with adhesive tape so that the step count cannot be read. The study nurse will verify the covered display a few times daily. The intervention group will receive an unblinded wristband. The handling of the activity trackers will be explained to the patients, and a predefined mobilization endpoint (step count) for the first 5 PODs will be targeted. The target step count was set at the 85% quartile on the basis of results a previous pilot study (Table 1). Patients older than 75 years of age were excluded from the analysis in the pilot study. The median age of this group was 60 years (IQR 52.5–70.5 years). A major pancreatic resection was performed in 35% of the patients, a major liver resection in 30%, a colorectal resection in 25%, and a gastric resection in 10%. A surgical fellow or a study nurse will assess and monitor the patient twice daily, between 9:00 a.m. and 11:00 a.m. and between 3:00 p.m. and 5:00 p.m., throughout the patient’s hospital stay to read the step count, to ensure its proper use and functioning, and to communicate the automatic feedback results. The study flowchart is shown in Fig. 1.

**Table 1 Tab1:** Mobilization targets in steps per day

	POD 1	POD 2	POD 3	POD 4	POD 5
Open surgery arm (*n* = 20)	500	620	800	1400	1400
Laparoscopic arm (*n* = 5)	1900	2300	2900	3400	3400

*POD* Postoperative day

Data are presented as 85% quartile based on *n* = 25 patients (results of a pilot study)

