### Study aim and objectives

The aim of the study is to increase the postoperative mobilization of the patients by giving them continuous feedback on their step count using activity-tracking wristbands. The primary endpoint of this study is the average step count in the first five POD in the intervention and control groups. Secondary endpoints are the percentage of patients in the two groups who master the predefined mobilization (i.e., step-count) targets, assessment of the activity data obtained from the devices (distance, activity time, inactivity, calorie consumption, compliance), assessment of preoperative mobility with the IPAQ [22], length of hospital and ICU stays (from the first POD until day of discharge), number of patients who receive physiotherapy, 30-day mortality, and 30-day overall morbidity according the Clavien-Dindo classification [23].

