### Statistical considerations and sample size calculation

The sample size estimation was based on our results in a pilot study with 30 participants, 25 of whom were analyzed to collect data about standard mobilization on the first 5 PODs following major visceral surgery. Based on those data, an increase in the daily step count by 250 steps/day with an SD of 290 steps/day was estimated. To achieve 80% power with a two-sided *P* value <0.05 and a dropout rate of 12%, the total sample size calculated with a two-tailed, unpaired *t* test was 120 patients with 30 patients in each group. 

The statistical analysis will be done on an intention-to-treat basis and will be performed with Statistical Package for Social Science software version 18.0 (SPSS, Chicago, IL, USA). The Mann-Whitney *U* test will be used to compare continuous variables, and Fisher’s exact test will be used for categorical variables. Two-sided *P* values will always be computed, and a difference will be considered statistically significant at *P* ≤ 0.05. The primary outcome is the average step count over the first 5 PODs of the patients in the intervention and control goups, separated into the laparoscopic and open surgery arms, respectively. Statistical testing of the outcome parameter will be performed using a regression analysis of repeated measures. In addition, the increase of mobilization within the groups will be analyzed using the repeated measures ANOVA. Logistic regression analyses will be computed to identify factors determining the patient cohort that achieved the mobilization targets (secondary endpoint). The following variables will be considered for the regression analysis: age, sex, body mass index (BMI), operative time, oncological versus nononcological indications, type of surgery (pancreatic, liver, intestinal, gastric), preoperative IPAQ score, and technique of surgery (laparoscopic versus open). Factors that are significant in univariate analysis will be further considered for a multivariate regression analysis.

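### The laparoscopic step targets are an 85th percentile of five patients, so attainment is not comparable between surgical arms and the attainment regression should not treat technique as a determinant

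*Protocol article*

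**What the plan says.** Under Randomization and procedures, the protocol article derives the targets from a pilot: "The target step count was set at the 85% quartile on the basis of results a previous pilot study (Table 1"). The footnote to Table 1 repeats the label for the whole pilot: "Data are presented as 85% quartile based on *n* = 25 patients (results of a pilot study"). The rows show how the 25 patients divide: "Open surgery arm (*n* = 20") and "Laparoscopic arm (*n* = 5"). From POD 1 to POD 5 the open targets are 500, 620, 800, 1400 and 1400 steps, and the laparoscopic targets are 1900, 2300, 2900, 3400 and 3400.

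The targets enter the analysis in two places.

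- Study aim and objectives lists as a secondary endpoint "the percentage of patients in the two groups who master the predefined mobilization (i.e., step-count) targets".
- Statistical considerations and sample size calculation adds: "Logistic regression analyses will be computed to identify factors determining the patient cohort that achieved the mobilization targets (secondary endpoint"). The candidate factors there include surgical technique, laparoscopic or open, and those significant in univariate analysis go forward to a multivariate model.

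The same section assigns Fisher's exact test to categorical variables and separates the primary outcome by surgical arm. It does not say whether attainment is separated too. The laparoscopic arm is 2 of 4 groups of 30, that is 60 of 120 planned patients.

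**The concern.** Table 1 puts the same percentile label on both rows, which invites the reading that the targets are equally hard in the two arms, each reached by about 15% of patients under standard care. A sample of five cannot support that. If the laparoscopic target happens to be much easier or harder than the open one, attainment will differ between the arms for that reason alone.

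The regression is where this can mislead. Technique can be a candidate factor only if both arms are in one model, yet the outcome in that model is defined differently by technique: on POD 1, success means 1900 steps for a laparoscopic patient and 500 for an open one. A technique effect could therefore be reported as a determinant of successful mobilization when it reflects the accident of five pilot patients.

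**Working it through.** **Inputs.** Percentile 0.85, n = 5 and n = 20, all from Table 1 and the text before it. Table 1 itself cannot be reproduced, because the article gives neither the raw pilot values nor the percentile definition. 85% is not a quartile; it is read here as the 85th percentile.

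**Step 1: which observation is the 85th percentile of five?**

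- Nearest rank: 5 × 0.85 = 4.25, rounded up to 5, the maximum.
- (n + 1)p: 6 × 0.85 = 5.1, capped at 5, the maximum.
- Linear interpolation, (n − 1)p + 1: 4 × 0.85 + 1 = 4.4, between the 4th and 5th values.
- Other common definitions give ranks from 4.25 to 4.87, also between the 4th and 5th values.

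The target is therefore the largest value or a weighted mean of the two largest.

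**Step 2: true standing of the laparoscopic target.** Let U be the true population percentile of the maximum of five independent values. For any continuous distribution P(U ≤ u) = u^5, which is Beta(5, 1).

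- Lower 2.5% point: 0.025^(1/5) = 0.478, so 1 − 0.478 = 52% would attain.
- Upper 97.5% point: 0.975^(1/5) = 0.995, so 1 − 0.995 = 0.5% would attain.
- Median attainment: 1 − 0.5^(1/5) = 13%.
- Chance that the maximum of five lies below the true 85th percentile: 0.85^5 = 44%.

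With linear interpolation (rank 4.4), simulation from normal and log-normal step counts gives about 2–3% to 59–61%. Interpolating does not remove the imprecision.

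**Step 3: the open target.** With (n + 1)p the rank is 21 × 0.85 = 17.85. Using Beta(17.85, 3.15) as an approximation for this fractional rank, the 95% range of the true percentile is 0.673 to 0.964, so about 4% to 33% attain. The exact ranges at ranks 17 and 18 are 6% to 38% and 3% to 32%. This is imprecise too, but much less so.

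| Arm | Pilot n | Nominal attainment per day | 95% range of true attainment per day |
|---|---|---|---|
| Laparoscopic (maximum of 5) | 5 | 15% | 0.5% to 52% |
| Open (rank 17.85 of 20) | 20 | 15% | about 4% to 33% |

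**Step 4: what this does to the technique coefficient.** Suppose both targets aim at the same true percentile, so that the correct odds ratio for technique is 1. Draw laparoscopic attainment from Beta(1, 5) and open attainment from Beta(3.15, 17.85), and form the ratio of the odds. Pilot sampling error alone puts this ratio beyond 2-fold in one direction or the other in 62% of draws, with a 95% range of 0.03 to 11. This is the odds ratio built into the cut-offs, before any sampling error in the trial.

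**The case against.** The strongest reply is that the endpoint counts patients who reach step counts fixed in advance, and does not depend on those counts being a true 85th percentile. Randomization is 1:1 and stratified by surgery type, and nothing in the text makes the targets differ by randomized group. An easy or hard cut-off shifts the base rate and the information in the endpoint, but does not bias feedback against control. This stands in full. The primary endpoint, average step count, does not use the targets either.

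Other parts of the reply also stand, and rule out stronger readings that a reader might infer:

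- **That the endpoint has no meaning in half the trial.** It has a plain meaning as a fixed threshold. What is lost is the reading as better than 85% of standard-care patients, and comparability between arms.
- **That the laparoscopic target is the largest pilot value.** This depends on a percentile definition that the article does not give.
- **That the arms will be summed into one percentage.** The endpoint names two groups and leaves the layout open; pooling is possible, not stated. For the regression, pooling does follow from listing technique as a factor.
- **That the five laparoscopic patients are missing from the reported case mix** (35% pancreatic, 30% liver, 25% colorectal and 10% gastric). Those percentages give whole patients for n = 20 (7, 6, 5, 2), but counts of 9, 8, 6 and 2 out of 25 are 36%, 32%, 24% and 8%, which round to the same figures at the nearest 5%.
- **That the rule for combining five daily targets is a fault.** A condensed article may leave it to the full protocol or analysis plan.

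It can also be said that listing technique in the regression adjusts the other factors for cut-off difficulty. That is true only if technique passes the univariate screen, and it leaves the technique coefficient itself uninterpretable.

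**Conclusion.** The concern holds in a limited form. The laparoscopic targets are a very imprecise percentile estimate. If they are the maximum of five, true standard-care attainment on a given day could be about 0.5% to 52% rather than 15%, against roughly 4% to 33% in the open arm. Attainment is therefore not comparable between surgical arms, and the regression as described cannot separate an effect of technique from the difficulty of each arm's cut-off.

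The randomized comparison, the primary endpoint and the sample size are untouched. What is at stake is one secondary endpoint and one exploratory model.

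The ranges assume independent pilot patients who are comparable with the trial's standard-care patients in the same arm, and they describe a single day. The figure of 52% at the upper end rests on the maximum; under linear interpolation it would be about 60%. The odds-ratio range further assumes that both targets were meant to sit at the same percentile, as the common label in Table 1 implies.

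**What to change.** Keep the targets and the yes/no endpoint unchanged, and describe the targets as fixed pragmatic thresholds. Then make two changes to the analysis:

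1. Compare attainment between the randomized groups within each surgical arm, or with a test stratified by arm, in place of one pooled percentage and an unstratified Fisher's exact test.
2. Fit the attainment regression separately in each arm; or fit one model in which technique is always kept as a stratification term, exempt from the univariate screen and not interpreted as a determinant.

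Surgical arm is already the stratification factor, so no new data are needed. The cost is the loss of a single headline percentage and less precision in each arm-specific estimate, which rests on 30 instead of 60 patients per randomized group. Replacing the endpoint by steps as a percentage of the target is not advised: it would keep the same imprecise targets as denominators and largely repeat the primary endpoint.

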**Fig. 1 Fig1:**
[figure not shown]
Flowchart. *EPM* Enhanced Perioperative Mobilization trial, *POD* Postoperative day

### Study aim and objectives

The aim of the study is to increase the postoperative mobilization of the patients by giving them continuous feedback on their step count using activity-tracking wristbands. The primary endpoint of this study is the average step count in the first five POD in the intervention and control groups. Secondary endpoints are the percentage of patients in the two groups who master the predefined mobilization (i.e., step-count) targets, assessment of the activity data obtained from the devices (distance, activity time, inactivity, calorie consumption, compliance), assessment of preoperative mobility with the IPAQ [22], length of hospital and ICU stays (from the first POD until day of discharge), number of patients who receive physiotherapy, 30-day mortality, and 30-day overall morbidity according the Clavien-Dindo classification [23].

### Statistical considerations and sample size calculation

The sample size estimation was based on our results in a pilot study with 30 participants, 25 of whom were analyzed to collect data about standard mobilization on the first 5 PODs following major visceral surgery. Based on those data, an increase in the daily step count by 250 steps/day with an SD of 290 steps/day was estimated. To achieve 80% power with a two-sided *P* value <0.05 and a dropout rate of 12%, the total sample size calculated with a two-tailed, unpaired *t* test was 120 patients with 30 patients in each group. 

The statistical analysis will be done on an intention-to-treat basis and will be performed with Statistical Package for Social Science software version 18.0 (SPSS, Chicago, IL, USA). The Mann-Whitney *U* test will be used to compare continuous variables, and Fisher’s exact test will be used for categorical variables. Two-sided *P* values will always be computed, and a difference will be considered statistically significant at *P* ≤ 0.05. The primary outcome is the average step count over the first 5 PODs of the patients in the intervention and control goups, separated into the laparoscopic and open surgery arms, respectively. Statistical testing of the outcome parameter will be performed using a regression analysis of repeated measures. In addition, the increase of mobilization within the groups will be analyzed using the repeated measures ANOVA. Logistic regression analyses will be computed to identify factors determining the patient cohort that achieved the mobilization targets (secondary endpoint). The following variables will be considered for the regression analysis: age, sex, body mass index (BMI), operative time, oncological versus nononcological indications, type of surgery (pancreatic, liver, intestinal, gastric), preoperative IPAQ score, and technique of surgery (laparoscopic versus open). Factors that are significant in univariate analysis will be further considered for a multivariate regression analysis.

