**Methods/design:**

Patients undergoing elective open and laparoscopic surgery of the colon, rectum, stomach, pancreas, and liver for any indication will be included. Further inclusion criteria are age between 18 and 75 years, American Society of Anesthesiologists Physical Status class less than IV, and a signed informed consent form. Patients will be stratified into two subgroups, laparoscopic and open surgery, and will be randomized 1:1 for automatic feedback of their step count using an activity tracker wristband. The control group will have no automatic feedback. The sample size (*n* = 30 patients in each of the four groups, overall *n* = 120) is calculated on the basis of an assumed difference in step count of 250 steps daily (intervention group versus control group). The primary study endpoint is the average step count during the first 5 postoperative days; secondary endpoints are the percentage of patients in the two groups who master the predefined mobilization (step count) targets, assessment of additional activity data obtained from the devices, assessment of preoperative mobility, length of hospital and intensive care unit stays, number of patients who receive physiotherapy, 30-day mortality, and overall 30-day morbidity.

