### Randomization and procedures

Patients are to be screened for eligibility on the day of admission. After participants give their informed consent to participate in the study, the International Physical Activity Questionnaire (IPAQ) will be administered to assess the preoperative mobilization, and the patients will receive preoperative counseling before surgery.

To avoid bias due to differences between laparoscopic and open surgery, two arms will be built before randomization: a laparoscopic arm and an open surgery arm. The study population will be stratified by surgery type (open and laparoscopic surgery). The randomization (control group versus intervention group) will be performed intraoperatively after the surgeon has confirmed the resectability using a block randomization with fixed block sizes in a 1:1 allocation ratio. The randomization sequences will be generated using the R statistical software package (R version 3.1.3, R Foundation for Statistical Computing, Vienna, Austria). Block size will be kept confidential until completion of recruitment.

The wristband will be worn continuously after the operation to count the patient’s steps 24 h per day until the beginning of POD 6. The Polar Loop activity tracker with FlowSync and Polar Flow software will be used for activity tracking (Polar Electro GmbH, Büttelborn, Germany). The device has been approved by the Medical Devices Act (EU Medical Device Directive 93/42/EWG/CD 0537) and is recommended for medical use.

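### The stated t-test inputs give 27 patients per group (108 in all), not the 30 (120) reported as their result; the discrepancy is conservative

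*Protocol article*

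**What the plan says.** Under 'Statistical considerations and sample size calculation', the protocol article reports that, from pilot data, "an increase in the daily step count by 250 steps/day with an SD of 290 steps/day was estimated". It sets 80% power "with a two-sided *P* value <0.05", allows for 12% dropout, and concludes that "the total sample size calculated with a two-tailed, unpaired *t* test was 120 patients with 30 patients in each group". The Abstract (Methods/design) repeats the total, makes clear that there are four groups (feedback or control, within laparoscopic or open surgery), and says the size "is calculated on the basis of an assumed difference in step count of 250 steps daily". Under 'Randomization and procedures', patients are allocated "using a block randomization with fixed block sizes in a 1:1 allocation ratio", with stratification by surgery type, so the two groups within each surgical arm are planned to be equal.

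The sizing text mentions no rounding up, safety margin, nonparametric correction or adjusted significance level.

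**The concern.** Inputs, method and result all stand together in one short passage, so the result can be checked without any other document. The article presents 120 as the output of the t-test calculation, not as a number chosen above it. If the output does not follow, then an input, the method or an unreported step differs from what is written, and a reader cannot tell which. What is at stake is the accuracy of the planning statement: the size attributed to the calculation, and the power that the chosen size delivers.

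**Working it through.** **Inputs** (all from 'Statistical considerations and sample size calculation', unless noted)
- Difference δ = 250 steps/day; SD σ = 290 steps/day; standardised difference d = 250/290 = 0.862
- Two-sided α = 0.05; power 80%; unpaired t test
- Dropout 12%, so a fraction 0.88 remains evaluable
- Four groups (Abstract), 1:1 allocation ('Randomization and procedures')

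**Attempt to reproduce 30 per group and 120 in all**

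*Step 1, normal approximation.* n = 2(σ/δ)²(z₀.₉₇₅ + z₀.₈₀)² = 2 × (290/250)² × (1.960 + 0.842)² = 2 × 1.3456 × 7.849 = 21.1, so 22 per group.

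*Step 2, t test (noncentral t, 2n − 2 degrees of freedom, noncentrality d√(n/2)).* Power is 0.798 at n = 22 and 0.816 at n = 23. The solution is 22.13, so 23 evaluable per group.

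*Step 3, dropout.*

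| Basis | Evaluable per group | Inflation | Enrolled per group | Total (×4) |
|---|---|---|---|---|
| t test | 23 | 23/0.88 = 26.1 | 27 | 108 |
| t test, multiplying instead | 23 | 23 × 1.12 = 25.8 | 26 | 104 |
| Normal approximation | 22 | 22/0.88 = 25.0 | 25 | 100 |

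None of these gives 30. Pooling the two surgical arms moves further away: 27 in each of two groups, 54 in all. Reaching 30 from 23 would need a dropout rate of 1 − 23/30 = 23%, not 12%.

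**Size of the gap.** 30 − 27 = 3 per group; 120 − 108 = 12 in all; 12/108 = 11%.

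**Power that 30 per group delivers on the stated inputs.** 30 × 0.88 = 26.4 evaluable per group. For the t test within one surgical arm:
- 26 evaluable per group: 0.862
- 26.4 evaluable per group: 0.867
- 30 evaluable per group (no dropout): 0.907

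**What would lead to 30.** Several different things would, and the article states none of them: plain rounding up from 27; a target power of 85% (26 evaluable, and 26/0.88 = 29.5, so 30); a somewhat larger SD (about 316 gives 80% power at 26 evaluable); or sizing for another test with an efficiency allowance.

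**The case against.** The strongest reply is that nothing has gone wrong for the trial. The text sets out to achieve 80% power, and 30 per group does so. Rounding up to 30 is an ordinary choice, and a journal article that condenses a full protocol may drop that step. Most of this stands: it settles that the consequence is small and that enrolment needs no change. It does not rescue the sentence, which attributes 120 to the t-test calculation itself.

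A second reply is that putting 86% in print could mislead, because it depends on one SD of 290 for both surgical arms and on a t test, whereas the primary outcome is to be tested by repeated-measures regression. Table 1 shows much higher step targets in the laparoscopic arm than in the open arm, and the article gives no SD by arm. Purely as illustrative assumptions, with 26 evaluable per group the t-test power would be about 60% at an SD of 400 and about 42% at 500. This stands as a reason to attach the conditions to any power that is quoted.

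A reader might also infer more than the article supports, in three ways:
- *That the stated power is wrong or cannot be checked.* It can be checked, and 80% is met as a minimum.
- *That the 30 came from a rank test,* since the Mann-Whitney test is named for continuous variables. Such a calculation can give 30, but so can 85% power or simple rounding, and nothing in the text favours one of them.
- *That the excess was meant to cover testing in two surgical arms at a split significance level.* The article sets a single 0.05 level and mentions no split, so the mismatch says nothing on that question.

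**Conclusion.** The point holds as an arithmetic error in the sample size statement. The stated inputs require 23 evaluable and 27 enrolled per group, 108 in all, against the reported 30 and 120. The error is conservative: on the article's own assumptions the t test has about 86% power within each surgical arm after 12% dropout, so this mismatch does not leave the trial short of its 80% target. These figures rest on the stated difference and SD holding in both surgical arms, equal group sizes, and dropouts contributing nothing to the comparison. Its weight is that of a reporting correction; no planned analysis or enrolment target changes because of it.

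**What to change.** Keep 120. Reword the sentence to say that the stated t-test calculation gives 27 per group (108 in all) after allowing for 12% dropout, and that 30 per group (120) was chosen. Name the actual basis for that choice, whether rounding or a margin, a higher target power, or a different test; only the investigators can supply it. If a power is quoted for the chosen size, give about 86% per surgical arm and say that it is conditional on the SD of 290 and on the t test. The cost is one corrected sentence, with no effect on recruitment, which has been under way since July 2016.

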
The present trial includes many types of operations, including hepatopancreatic, GI, and colorectal surgery, which might have a different impact on the patients’ postoperative physiology and ability to ambulate. This broad range of operations was intended to increase the applicability and generalizability of the study. As a result, minor effects of the activity-tracking feedback that might be confined to only one type of surgery might be missed. However, our pilot study, although not powered for this endpoint, showed no significant difference in the achieved postoperative step counts between the different operations.

The present study further includes patients within a broad age range and associated fitness level. Differences in functional abilities naturally occurring with aging [33] and that might be aggravated after surgery can further bias the study, but they might contribute to the applicability of the results. In addition, the potential for discrepancies between the self-reported preoperative mobility assessed by the IPAQ and actual quantitative mobility cannot be excluded. In addition, the IPAQ was not designed for patients in a hospital setting (i.e., inpatients). Nevertheless, the IPAQ is considered an appropriate tool to assess physical activity in daily life, and results derived from it will be analyzed as a secondary endpoint in the present trial [34].

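### Where open and laparoscopic patients are combined, the named tests carry no stratum term, and the pre-randomization IPAQ is labelled a secondary endpoint rather than used as a prespecified covariate

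*Protocol article*

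**What the plan says.** All places are in the protocol article.

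- **Stratification.** Under Randomization and procedures: "The study population will be stratified by surgery type (open and laparoscopic surgery". The reason given is to avoid bias from differences between the two approaches.
- **General tests.** Under Statistical considerations and sample size calculation, the Mann-Whitney U "test will be used to compare continuous variables", and Fisher's exact test serves for categorical variables. Neither is given a stratum.
- **Primary outcome.** The same section separates average step count over five days by approach and tests it with a repeated-measures regression. The article does not list the model terms.
- **Secondary endpoints.** Under Study aim and objectives, target attainment is compared between two groups. Device activity data and length of stay are listed with no split by approach.
- **IPAQ.** It is given after consent, before surgery; randomization follows intraoperatively. The endpoint list nevertheless includes "assessment of preoperative mobility with the IPAQ", and the Discussion adds that "results derived from it will be analyzed as a secondary endpoint in the present trial".
- **Covariates.** IPAQ score and surgical technique are among the candidate variables for a regression. In context this is the logistic model of who reaches the step targets: the list follows directly on that model and omits treatment allocation. Factors enter the multivariable model only if significant univariately.

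**The concern.** A stratification factor is chosen because it predicts outcome. If the analysis then combines the strata without a stratum term, the difference between approaches stays in the error variance. Allocation has already balanced that difference, so the usual standard error is too large: the test is conservative and real effects are harder to detect. The protocol itself expects the approaches to differ, since Table 1 sets separate step targets for each.

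IPAQ raises a related point. Feedback cannot alter a measurement taken before randomization, so IPAQ carries no information about the treatment effect as an outcome. It is the one baseline measure of physical activity that the article names, and its natural use is to sharpen the treatment comparison. The text instead calls it an endpoint and offers it only to a screened prognostic model. What is at stake is precision, not validity.

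**Working it through.** **1. The plan's own sample size.** Inputs from Statistical considerations and sample size calculation: "an increase in the daily step count by 250 steps/day with an SD of 290 steps/day was estimated"; "To achieve 80% power with a two-sided" 5% level; "and a dropout rate of 12" per cent. Standardized difference = 250/290 = 0.862. The unpaired t test needs 22.1, so 23 per group; 23/0.88 = 26.1, so 27 per group, or 4 × 27 = 108. The plan states 30 and 120. The difference is on the generous side and is a separate matter. With 30 per group, 30 × 0.88 = 26.4, so about 26 are evaluable per cell, and t-test power within one approach is 86%.

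**2. Effect of pooling approaches.** Two approaches with 26 evaluable per cell give 52 versus 52. With within-approach SD 290 and a mean gap g between equal-sized strata:

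pooled SD = √(290² + (g/2)²)

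For g = 1836: √(84,100 + 842,724) = 963.

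The van Elteren statistic sums (W − E)/(N + 1) over strata, divided by the square root of the summed V/(N + 1)², where W is the rank sum and E and V are its null mean and variance within the stratum. Simulation with normal data and shift 250:

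| Assumed gap (steps) | Pooled SD | Power, pooled Mann-Whitney | Power, van Elteren | Type I error, pooled |
|---|---|---|---|---|
| 0 | 290 | 99% | 99% | 4.6% |
| 250 | 316 | 98% | 99% | 2.9% |
| 500 | 383 | 94% | 99% | 0.7% |
| 1000 | 578 | 66% | 99% | about 0% |
| 1836 | 963 | 56% | 99% | about 0% |

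Repeat simulations differ by up to about 2 points.

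**3. Where the gap comes from.** The documents give no mean gap. The largest value is the difference between the Table 1 averages: open (500 + 620 + 800 + 1400 + 1400)/5 = 944; laparoscopic (1900 + 2300 + 2900 + 3400 + 3400)/5 = 2780; difference 1836. These are 85% quantiles from 20 open and 5 laparoscopic pilot patients, so 1836 only stands in for a mean gap.

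Nor do the documents say that 290 is a within-approach SD. If it were the overall SD of those 25 patients, a mean gap g alone would contribute √(0.8 × 0.2) × g = 0.4g. At 1836 that is 734, which exceeds 290, so g could be at most 290/0.4 = 725. The table is therefore a range, not an estimate.

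**4. Effect of adjusting for IPAQ.** With correlation r between IPAQ and step count, residual SD = 290 × √(1 − r²). The documents do not give r. Within one approach, 26 per group:

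| Assumed r | Variance removed | Residual SD | Power |
|---|---|---|---|
| 0 | 0% | 290 | 86% |
| 0.2 | 4% | 284 | 88% |
| 0.3 | 9% | 277 | 89% |
| 0.4 | 16% | 266 | 91% |
| 0.5 | 25% | 251 | 94% |

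**The case against.** The strongest reply is that the plan does respect the stratum where it matters most. The primary outcome is separated by approach, the trial is sized at 30 in each of four cells, and step targets are set per approach. A within-approach comparison carries no difference between approaches as noise. This stands. A reader might infer that the primary analysis ignores the stratum and that its power drops to 56% (Mann-Whitney) or 26% (pooled t test at a gap of 1836). The documents do not support that: those figures describe a pooled test that is not the stated primary analysis, at the far end of an assumed range.

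Three further replies also stand:

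- The article's silence on the terms of the primary regression does not show that they are absent. A fuller protocol or analysis plan may give them.
- No sentence says that IPAQ will be tested between arms. The error is the label and the use, not a stated test.
- The Discussion warns that self-reported IPAQ may differ from actual mobility and was not designed for inpatients, so a weak correlation is plausible. At 0.2 the gain is about 2 points.

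Two things are not answered. The general tests for secondary endpoints are stated without a stratum, and separation by approach is stated only for the primary outcome. IPAQ is called an endpoint twice, and the only covariate rule given lets both IPAQ and approach be dropped on a univariate P value.

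**Conclusion.** The point holds for secondary endpoints analysed across both approaches and for the role given to IPAQ. It should be corrected, but it does not threaten the validity of the trial. A pooled test after stratified allocation loses power without producing false positives.

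On the step scale the loss is negligible up to a gap of about 250 steps, about 5 points at 500, and 33 to 43 points at 1000 to 1836. This assumes normal data, a within-approach SD of 290 and 26 evaluable per cell. The loss for length of stay cannot be derived from the documents. For target attainment it may be small, because the targets are already specific to each approach. The IPAQ gain of about 2 to 8 points rests on assumed correlations of 0.2 to 0.5.

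**What to change.** 1. Wherever the approaches are combined, replace the plain tests with van Elteren (continuous) and Cochran-Mantel-Haenszel (categorical) tests, or use a regression with a term for approach.
2. In the primary repeated-measures regression, name preoperative IPAQ as a prespecified covariate, and add approach as a term if the strata are analysed together. Exempt both from univariate screening.
3. Move IPAQ from the secondary endpoints to the baseline characteristics, in the endpoint list and in the Discussion.

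If a fuller analysis plan already does this, it is enough to align the article's wording with it. All variables are already collected, so the cost is analysis wording only, with no change to recruitment, procedures or sample size. The change should be dated before group data are examined.
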